#### 7.4.2 Disease-Modifying Analysis

If there is evidence from the primary analysis that Simvastatin is not futile, consideration will be given to performing additional analysis of the primary outcome to investigate a potential disease-modifying effect. Descriptive statistics (e.g. means and 95% CI) and plots of MDS-UPDRS part III by visit month and allocated group will be presented. Participants will be included in the disease modifying analysis if: (i) they have fully complied with the treatment protocol (i.e. definition (i) from section 4.4.2) and (ii) they have provided valid MDS-UPDRS III scores at least two time points according to the imputation requirements outlined in section 4.10.1.

A mixed effects, repeated measures model will be fitted to the primary outcome measured at baseline, 12, 24 and 26 months, with participants included as a random effect. This repeated measures model will allow for missing data, whilst also allowing for analysis of the two-period design of the washout phase.

Adjustments will also be made for the stratification variables, modified Hoehn & Yahr score as a fixed effect and recruiting site as a random effect, as well as patient-related factors, which may have a strong influence on disease progression, i.e. disease duration, gender and age at baseline, to account for potential influence on the primary outcome.

The repeated measure model to investigate a disease modifying effect is defined as

$$y_{i,j,t} = \delta^{12*} x_{1,i,j} I_{t=12} + \delta^{24*} x_{1,i,j} I_{t=24} + \delta^{26*} x_{1,i,j} I_{t=26} + \delta_1 t + \theta x_{i,j} + Z_i + U_{i,j} + \varepsilon_{i,j,t}$$

Equation 5

where  $\delta^{k*}$  is the allocated group difference at the  $k$  visit month. The terms  $y_{i,j,t}$ ,  $x_1$ ,  $\delta_1$ ,  $x_{i,j}$ ,  $\theta$ ,  $Z_j$ ,  $U_{i,j}$ ,  $\varepsilon_{i,j,t}$ ,  $I_{t=k}$ ,  $i$  and  $j$  are the same as defined in Equation 4, but  $k = 12, 24, 26$ , which include the 26-month visit and excludes baseline.

The study is not powered to determine whether the treatment is disease modifying. Therefore, the results of this analysis should be treated with caution, and interpreted as exploratory only. However, interpretation will focus on  $\delta^{26*}$ , where an estimate below zero may be indicative of a effect that persists after discontinuation of treatment, suggesting the possibility that the effect of simvastatin is disease modifying rather than merely symptomatic.

The duration of the washout period of two months was a pragmatic decision. Currently there is no literature defining an appropriate washout period that would ensure any potential symptomatic effect of Simvastatin on PD had completely disappeared.

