| SAP Clarifications | 
 
(i) To maximise all available data, the disease-modifying analysis will use the compliance definition exactly as specified in section 4.4.2(i), such that the <math>\pm 2</math>-week visit window only applies to the 24-month follow-up visit.
 
(ii) In section 6.2 the adjustment for the modified Hoehn and Yahr score will be conducted according to the cut-off used to stratify the randomisation procedure (i.e. <math>\leq 2.0</math> versus 2.5-3.0).
 
(iii) For all 24-month group comparisons in which the model adjusts only for baseline (as per section 6.2), random effects for centre will not be included.
 
                                                                                                                                                                                                                                                                                                                                                                                                                                                                                                                                                                                                                                                                                                                                                                                                |         |                                                                                                        |

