### 3.3 ANALYSIS POPULATIONS

We will base the primary analysis of the primary outcome on a modified intention-to-treat (mITT) principle. The mITT evaluable sample for the primary analysis will include all participants who are randomised, provide baseline outcome data, commence to the higher dose phase of the study and provide 24-month outcome data. Imputation will only be performed for missing questionnaire items that fulfil pre-specified criteria as outlined in section 4.10.

To investigate any effect of compliance with taking study medication, if  $\geq 20\%$  of participants in the active Simvastatin group are identified as non-compliers (according to each of the definitions in section 4.4.2), we will undertake additional sensitivity analyses of the primary outcome (further details in section 7.3.1). This population will consist of all participants with baseline and 24-month primary outcome data.

The safety population will consist of all participants who have at least one dose of allocated trial treatment.

A washout period has been included in the study design to explore the potential disease-modifying effect of Simvastatin. Trial treatment will be discontinued at 24 months and a follow-up visit is conducted two months later at 26 months post-baseline. All participants still on trial treatment at the higher dose of 80mg at 24 months with valid baseline, 24 and 26 months data will be included in the disease-modifying analysis.

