#### **4.4.2 Protocol Violation or Deviation**

Non-compliance may occur in some instances if participants do not complete their allocated treatment according to the study protocol, or if the follow-up visit was not within  $\pm 2$  weeks of the scheduled date. This could occur because of medical issues such as fatigue, deterioration of health, acceleration of PD, difficulty in attending outpatient clinics in the OFF state, or participants may simply decide that they no longer want to complete the programme.

Within the PD STAT study protocol (section 17.9), there is allowance for study drug dose alterations, depending on whether the patient is at the initial low dose phase or high dose phase. If a participant discontinues treatment during the low dose phase, attempts will be made to recruit an additional participant. During the high dose phase, participants with unwanted symptoms/side effects may reduce to the 40mg dose and then may continue on the 40mg dose for the remainder of the trial or, at the discretion of the local investigator, such participants may later be re-challenged with the 80mg dose after resolution of the unwanted symptoms. Participants who are on the 80mg dose and subsequently fulfil the trial stopping criteria will be withdrawn from treatment but invited to continue with the study assessments.

Complete identification of compliance with the study protocol may not be possible. For example, there may be unreported instances where participants miss doses of their medication or medication containers are not returned. Compliance will be assessed based on a combination of each participant's self-reported compliance during telephone calls and capsule count, but this may not capture the participant's true compliance. Therefore, we will base compliance on the reported data, acknowledging it may have limitations. Figure 1 outlines the possible forms of non-compliance we will be able to identify through the data collected.

We have constructed two definitions of study compliance. These are:

- (i) Participants are compliant only if they proceed to and maintain the 80mg dose and attend 24 month follow-up within their 2-week window of their due date, and non-compliant if they remain on the 40mg dose, discontinue trial treatment or attend the 24-month follow-up visit outside of the 2-week window.

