#### **7.3.1 Non-Compliance Sensitivity Analysis**

Frequency and percentages of non-compliers for each of the compliance definitions outlined in section 4.4.2 will be reported. If  $\geq 20\%$  of participants with 24-month outcome data are classed as non-compliers based on either compliance definition (i) or definition (ii) from section 4.4.2, a sensitivity analysis based on that definition will be triggered. Therefore, a maximum of two non-compliance sensitivity analyses will be performed.

One potential method for sensitivity analyses is a per protocol analysis, which would only analyse participants who completed the trial as indicated in the protocol. However, this approach could introduce bias by excluding participants after randomisation and thus jeopardising the group comparability achieved through randomisation.

As an alternative, a complier-average causal effect (CACE) analysis will be undertaken if triggered according to the criteria above, which will provide an unbiased estimate of the intervention effect, based on protocol compliance. In a CACE analysis, participant's allocated group is included in the model as an instrumental variable and the participant's given treatment is an endogenous variable, which will consist of placebo or intervention. The definitions of compliance in section 4.4.12 will be used to determine the participants' given treatment.

Under compliance definition (i), intervention participants' given treatment (the endogenous variable) would remain as intervention only if they proceeded to and maintained the 80mg dose and attended their 24-month follow-up assessment within the 2-week window. If they did not proceed to the 80mg dose, or if they did not attend their 24-month follow-up within the 2-week window, they would be classed as non-compliers and their given treatment would be classified as placebo.

Compliance definition (ii) is less stringent than compliance definition (i); participants in the intervention group will be classed as compliers and their given treatment will remain as intervention even if they do not proceed to the 80mg dose, provided they attend their 24-month assessment within the 2-week window and at least remain on the 40mg dose. Otherwise, their given treatment will become placebo.

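### The only planned model of the 26-month data is restricted to full compliers, so selection after randomisation can bias its between-group difference in either direction, and no wider-set fit stands beside it

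*SAP*

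**What the plan says.** Section 7.4.2 sets two entry conditions for the disease-modifying model. The first is that "they have fully complied with the treatment protocol (i.e. definition (i) from section 4.4.2"); the second is valid MDS-UPDRS part III scores at two or more time points. Definition (i) in section 4.4.2 begins "Participants are compliant only if they proceed to and maintain the 80mg dose and attend 24 month follow-up within their 2-week window of their due" (the quote stops just before the clause ends). SAP Clarification (i) confirms the choice: "the disease-modifying analysis will use the compliance definition exactly as specified in" section 4.4.2(i), with the visit window applying to month 24 only.

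The coefficient of interest is the Simvastatin-minus-placebo difference at 26 months. An estimate below zero is read as a possible effect that outlasts treatment. The analysis is labelled exploratory, the stated reason being that the study is not powered for it. It is considered only if the primary analysis does not show futility.

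On per-protocol analysis of the primary outcome, section 7.3.1 says that "this approach could introduce bias by excluding participants after randomisation and thus jeopardising the group comparability achieved through randomisation", and a complier-average causal effect (CACE) analysis is planned instead.

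On why participants become non-compliant, section 4.4.2 says "This could occur because of medical issues such as fatigue, deterioration of health, acceleration of PD", among other reasons.

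Section 3.3 describes the disease-modifying set differently: "All participants still on trial treatment at the higher dose of 80mg at 24 months with valid baseline, 24 and 26 months data".

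**The concern.** Maintaining 80mg and attending month 24 in window are both settled after randomisation. Restricting the model to participants who did both compares two selected subgroups. That is the objection 7.3.1 raises, yet 7.4.2 neither repeats it nor plans a counterpart.

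No other planned model fills the gap. Equation 4 in section 7.4.1 stops at 24 months. Section 8 models secondary outcomes at 24 months, or over baseline, 12 and 24 months. The COVID-19 sensitivity analysis in 7.4.2.1 refits Equation 5 without naming a wider set. Section 7.4.2 plans descriptive summaries by allocated group, but the reading rests on the model coefficient. Secondary objective ii, separating symptomatic from disease-modifying effects, therefore has no model-based 26-month estimate that keeps the randomised comparison.

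Section 7.4.2 notes that the repeated-measures model allows for missing data. That covers missed visits among participants in the data set. It cannot bring back participants who were removed from it.

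**Working it through.** **Is the selection related to outcome or arm?** Section 4.4.2 lists "medical issues such as fatigue, deterioration of health, acceleration of PD, difficulty in attending outpatient clinics in the OFF state" and also the participant's own decision to stop. Some of these reasons depend on progression and some need not. Side effects are a route to 40mg, which makes a participant non-compliant under definition (i), but the text does not link them to progression. No reason is tied to an arm. Outcome-related selection is therefore plausible, and its difference between arms is unknown.

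**The plan's own figures.** The SAP gives no non-compliance rate for this set. Its sample size reproduces: difference 3, SD 7.5, one-sided alpha 10% and power 80% give 56.3, so 57 per group; 57/(1 - 0.15)² = 79; 79/(1 - 0.2) = 99; total 198. The point does not turn on these numbers, but SD 7.5 and 79 per arm are used below.

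**Shift from selection, with no true effect.** Let q be the share of an arm excluded and rho the correlation between being excluded and progressing faster. The mean of those kept moves by

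shift = -rho × 7.5 × phi(z(1-q))/(1-q),

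where phi is the standard normal density and z(1-q) the standard normal quantile. The bias is the Simvastatin shift minus the placebo shift. All q and rho are assumptions, and the SD of 24-month change stands in for that at 26 months.

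Worked example, 20% versus 10% excluded, rho 0.3 in both arms:
- Simvastatin: -0.3 × 7.5 × 0.280/0.8 = -0.79
- placebo: -0.3 × 7.5 × 0.1755/0.9 = -0.44
- bias: -0.79 + 0.44 = -0.35

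| Simvastatin q, rho | Placebo q, rho | Bias (points) | Simulated |
|---|---|---|---|
| 20%, 0.3 | 20%, 0.3 | 0.00 | 0.01 |
| 20%, 0.3 | 10%, 0.3 | -0.35 | -0.33 |
| 30%, 0.3 | 10%, 0.3 | -0.68 | -0.67 |
| 20%, 1 | 10%, 1 | -1.16 | -1.11 |
| 15%, 1 | 0% | -2.06 (extreme) | not run |
| 30%, 0 | 10%, 0.3 | +0.44 | +0.44 |
| 30%, 0.1 | 15%, 0.5 | +0.66 | not run |
| 20%, -0.3 | 10%, -0.3 | +0.35 | +0.33 |

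The simulated column comes from 4,000 runs of Equation 5 with 79 per arm, an assumed baseline SD of 10 and no site effect. Monte Carlo error is 0.02.

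**The two descriptions of the set.** A participant with valid baseline and 24-month scores but no 26-month score can enter under 7.4.2 and not under 3.3. A participant on 80mg at month 24 who attended outside the window, with all three scores, enters under 3.3 and not under 7.4.2. Clarification (i) supports 7.4.2, but 3.3 still stands.

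**The case against.** The restriction serves the washout question. Someone who stopped early has no change from on-drug to off-drug between months 24 and 26, so a wider set describes washout less cleanly. This stands, and it is why the wider fit should not be the sole basis of interpretation.

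Section 7.3.1 says only that per-protocol analysis could introduce bias, and says so about the primary outcome. The 26-month analysis is exploratory and conditional, and no decision rule rests on it. This also stands and limits the severity. It does not answer the point, because lack of power concerns precision, whereas selection moves the estimate.

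Some reporting exists already. Section 4.4.2 plans counts and details of non-compliers by arm, and Equation 4 has no compliance restriction, so selection at months 12 and 24 can be gauged by comparison. Neither gives a 26-month estimate in the wider set.

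A reader might infer that the exclusions push the result towards false neuroprotection. The SAP does not support that. It needs Simvastatin exclusions to remove faster progressors more often or more strongly than placebo exclusions do, and the SAP gives no rates by arm. If Simvastatin exclusions are mainly for tolerability and placebo exclusions follow progression, the bias runs against Simvastatin. Nor can the SAP's 15% and 20% serve as exclusion rates here: one is assumed stopping in the low-dose phase, the other the CACE trigger.

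A reader might also judge the harm by how far the chance of an estimate below zero rises above 50% under no effect. That ignores the condition for running the analysis. With 79 per arm, SE = 7.5 × sqrt(2/79) = 1.19, and a not-futile result needs a 24-month estimate below about -1.47, which has a chance of about 11% under no effect. Given that, and an assumed correlation of 0.6 to 0.8 between the 24- and 26-month estimates, the chance of a negative 26-month estimate is already about 89% to 98% without selection bias. A bias of -0.45 (20% versus 10% excluded, those excluded progressing 4.5 points worse: -0.10 × 4.5) raises it only to about 95% to 99.5%.

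**Conclusion.** The point holds as a moderate one. The only planned between-group model of 26-month data rests on a post-randomisation selection that the SAP itself distrusts elsewhere. No wider-set fit is planned, and selection is not named as a limitation.

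The resulting bias has no established size or sign: zero with equal selection, and about -2.1 to +0.7 points over the patterns tried, against a 3-point futility margin. The negative end is an extreme case in which only Simvastatin participants, and exactly the fastest progressors, are excluded. At rho 0.3 in the same direction in both arms, with 20% or 30% of Simvastatin and 10% of placebo excluded, the bias is -0.35 to -0.68. These ranges rest on assumed exclusion rates and correlations, on SD 7.5, and on definition (i) being applied to both arms as worded. The mismatch between 3.3 and 7.4.2 rests on no assumption.

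**What to change.** In section 7.4.2:

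- Also fit Equation 5, by allocated group, to all randomised participants with available OFF scores, regardless of dose reduction, discontinuation or the month-24 window. Report it beside the complier fit.
- Read a 26-month difference below zero as possible disease modification only if both fits agree.
- Name post-randomisation selection as a limitation alongside lack of power.
- Report the number excluded from this set, with reasons, by arm.
- Reconcile the set in 3.3 with that in 7.4.2 so that one definition applies.

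The cost is SAP wording and one more fit of the same model. No new data collection is needed, since sections 4.4.2 and 5.1 already invite or encourage those who stop treatment to continue assessments. The drawback is that the wider-set estimate includes participants already off drug before month 24, so it is diluted as a description of washout. That is the reason to keep both fits.

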Hence  $\alpha$  and  $\beta$  were chosen to reflect the futility design-based hypotheses, with the one-sided  $\alpha$  set at 10% and  $\beta$  at 20% (i.e. 80% power).

Based on a recently reported study at the time of the design of this futility trial, the expected mean increase in MDS-UPDRS part III from baseline to 12 months in the placebo group is assumed to be 2.2 points, with corresponding standard deviation of 7.3 points. Assuming that this increase in MDS-UPDRS part III is linear over time, gives an expected mean increase from baseline to 24 months of 4.4 points in the placebo group (i.e.  $\mu_p = 4.4$ ). Therefore, if we assume the MCID is -3, this implies the mean of the Simvastatin group,  $\mu_s$ , is 1.4 points. Additionally, we assume a slightly inflated standard deviation over this period of 7.5 points.

The sample size calculation was based on a two-sample t-test with a 10% one-sided alpha. Following the previously listed assumptions, the number of participants needed to follow-up at 24 months (i.e. with primary outcome data) is 57 participants per group, to provide 80% power to reject the null hypothesis of non-futility and declare futility.

This sample size was inflated to allow for a proportion of participants allocated to the Simvastatin group to stop taking the trial medication during the initial 1-month low dose phase. Assuming that this proportion was 15%, the above sample size was inflated by  $(1-0.15)^{-2}$ , to give 79 participants per group. Secondly, the sample size was adjusted to allow for a (non-differential) loss to follow-up rate of 20%. Accordingly, the sample size was further inflated by a factor of  $(1-0.2)^{-1}$ , to give a sample size of 99 participants per group and a total recruitment target of 198 participants commencing the higher dose phase of the study.

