### 7.2.1 Interpretation of the results of the primary analysis

The primary analysis aims to determine the futility, or otherwise, of Simvastatin with respect to the primary outcome. Recall the hypotheses in section 4.2:

$$H_0: \mu_s - \mu_p \leq -3 \text{ versus } H_1: \mu_s - \mu_p > -3.$$

Testing of this will be achieved by determining whether the adjusted treatment coefficient estimate,  $\delta_s$  from Equation 2, is less than or equal to -3, based on the test statistic from chapter 8 in Ravina, et al.:

$$\frac{\delta_s - (-3)}{\sigma_s} \sim t_\eta$$

Equation 3

where  $\sigma_s$  is the standard error for the estimated coefficient and  $t$  is student's  $t$  distribution with  $\eta$  degrees of freedom. The degrees of freedom ( $\eta$ ) is calculated from the total sample size minus the number of treatment groups minus number of adjustment covariates. The  $p$ -value for this test is determined by examining the upper tail of student's  $t$ -distribution. Possible scenarios for the futility analysis of Simvastatin are presented in Figure 2.

[figure not shown]

Figure 2: Possible scenarios for observed group differences in the change of MDS-UPDRS between baseline and 24 months under the assumptions of a futility analysis. The black circles are the between group differences in change in UPDRS at 24 months (point estimate). The red lines are two-sided 80% confidence intervals if the study is futile (i.e.  $p < 0.1$ ) and blue lines are two-sided 80% confidence interval if the study is non-futile (i.e.  $p \geq 0.1$ ). The dashed grey line at -3 is the pre-specified minimal clinically important difference. The dotted grey line at CV is the critical value from student's  $t$ -distribution; the point estimate should be above this value (to the right of this line) to demonstrate futility.

If the  $p$ -value is less than 0.1, then the null hypothesis (that Simvastatin is not futile) will be rejected and Simvastatin will not be recommended for a phase III study. If the  $p$ -value is greater than 0.1 then there is insufficient evidence to reject the null hypothesis that Simvastatin is not futile.

| P-value | 80% Confidence Interval | Recommendations                                                                                                                                                                                                    |

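### Sections 3.3 and 7.4.2 define different analysis sets for the disease-modifying analysis, and 7.4.2 attaches its exploratory reading to the sign of the 26-month estimate alone

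*SAP*

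**What the plan says.** **Who is analysed.** SAP 3.3 takes participants still on trial treatment at 80mg at 24 months, "with valid baseline, 24 and 26 months data will be included in the disease-modifying analysis". SAP 7.4.2 sets two other conditions for the same analysis: compliance under definition (i) of 4.4.2, and that "they have provided valid MDS-UPDRS III scores at least two time points according to the imputation requirements" of 4.10.1. Definition (i) requires that 80mg was reached and maintained and that the 24-month visit fell within two weeks of its due date. Clarification (i), in the administrative information, confirms definition (i) for this analysis, with the window applying to the 24-month visit only. It mentions neither 3.3 nor the number of valid scores.

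**When it is done.** "If there is evidence from the primary analysis that Simvastatin is not futile, consideration will be given to performing additional analysis" of the primary outcome. Under 7.2.1, a p-value above 0.1 means that "there is insufficient evidence to reject the null hypothesis that Simvastatin is not futile".

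**How it is read.** The study is said not to be powered for this question, and "the results of this analysis should be treated with caution, and interpreted as exploratory only". The text then puts the interpretation on the 26-month group difference (delta26* in Equation 5), "where an estimate below zero may be indicative of a effect that persists after discontinuation of treatment". No interval, threshold or comparison with the 24-month difference (delta24*) is tied to that reading. The section adds that the two-month washout was pragmatic and that no literature defines a period sure to clear a symptomatic effect.

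**The concern.** Secondary objective (ii) in 2.2 is to distinguish symptomatic from disease-modifying effects, and this analysis serves it.

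First, two analysts who follow the SAP faithfully could analyse different people. Choosing between the sets after unblinding is the freedom that a SAP should remove.

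Second, the sign of an estimate carries little information. If nothing persists at 26 months, an estimate is as likely to fall below zero as above it. The analysis is also entered only after a 24-month result favourable enough to avoid futility. The 24- and 26-month estimates come from largely overlapping participants and are presumably positively correlated, so a negative 26-month estimate becomes more likely still without any persisting effect.

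**Working it through.** **1. The two sets side by side**

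| Participant | 3.3 | 7.4.2 |
|---|---|---|
| On 80mg throughout, all scores valid, 24-month visit outside the window | in | out |
| Compliant under (i), valid baseline and 24-month scores, no valid 26-month score | out | in |
| Reduced to 40mg, re-challenged, on 80mg at 24 months, all scores valid | in | arguably out (80mg not maintained) |

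The second row will occur. Section 3.1.1 expects remote 26-month visits. Section 4.10.3 says that question 3 (5 items) and question 12 (1 item) of part III cannot be scored remotely: 5 + 1 = 6 missing. The postural tremor item omitted from the case report form usually makes it 7. The limit in 4.10.1 is three.

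**2. The plan's own figure**

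Inputs from 4.2: SD 7.5, margin −3. "The sample size calculation was based on a two-sample t-test with a 10% one-sided alpha", and the follow-up number is set "to provide 80% power to reject the null hypothesis of non-futility and declare futility".

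- n = 2 × 7.5² × (1.2816 + 0.8416)² / 3² = 56.35, so 57 per group (power 80.1% by the noncentral t).
- 57 / 0.85² = 78.9, so 79; 79 / 0.8 = 98.75, so 99 per group, 198 in total.

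The SAP's 57, 79 and 99 are reproduced. I use 57 (the number needed) and 79 (99 less 20% loss) as the range per arm.

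**3. Point at which futility is not declared**

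SE = 7.5 × √(2/n); futility is not declared when the 24-month estimate is below −3 + t(0.90) × SE. I use 2n − 2 degrees of freedom; subtracting the covariates as in 7.2.1 makes no material difference.

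- 57 per arm: SE 1.405, cut-off −3 + 1.289 × 1.405 = −1.19.
- 79 per arm: SE 1.193, cut-off −3 + 1.287 × 1.193 = −1.46.

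**4. Chance of a negative 26-month estimate when the true 26-month difference is 0**

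Treat the two estimates as bivariate normal with correlation ρ. The share sought is P(delta26* estimate < 0 | 24-month estimate below the cut-off). The SAP gives no ρ; I assume 0.3 to 0.9. Without the non-futility condition the answer is 50%. With it:

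| True 24-month difference | Non-futile, 57 / 79 per arm | Negative sign, 57 per arm | Negative sign, 79 per arm |
|---|---|---|---|
| 0 (never any effect) | 19.9% / 11.0% | 67–99% | 70–99.9% |
| −1.5, fully lost | 58.8% / 51.2% | 58–79% | 59–85% |
| −3, fully lost | 90.1% / 90.1% | 52–56% | 52–56% |

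The joint chance that an inert drug is both found non-futile and shows a negative sign is 13–20% at 57 per arm and 8–11% at 79.

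Simulating Equation 5 itself, with a baseline-adjusted 24-month comparison as the condition and variances assumed to give a change SD near 7.5, produced ρ of 0.59 to 0.88. Negative signs made up 86–99.7% in the no-effect case and 54–56% in the −3 case; without the condition, 48.5–51.1%.

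**5. The same condition with an interval**

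Replace the sign by a 95% CI for delta26* wholly below 0 (half-width 1.96 × SE: 2.75 points at 57 per arm, 2.34 at 79, if the 24-month SE applies). False readings are 2.5% unconditionally. After a non-futile result they are about 2.8% in the −3 case. In the no-effect case they are 5.5–12.5% at 57 per arm and 6.6–21.8% at 79.

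**6. Incomplete washout**

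If 1 of 3 symptomatic points remained at 26 months (illustrative), the sign would be negative in 78–88% of non-futile trials.

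**The case against.** The strongest reply is that 7.4.2 contains no decision rule. The analysis is discretionary, stated to be unpowered and exploratory, and worded as a possibility. No progression step depends on it. Equation 5 estimates delta24* and delta26* together, 7.4.2 also presents means with 95% CIs by visit and group, and 4.3 sets 95% intervals for other outcomes generally. This stands as a limit on weight. A reader might infer that the plan would declare disease modification from a sign; it would not. Caution still supplies no criterion, and the one criterion offered is the sign.

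Other stronger readings also fail:

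- **That the no-effect figures near 100% are an overall error rate.** They apply only after an inert drug has escaped futility, which happens 11–20% of the time, and the top values need ρ near 0.9. With a true −3 effect at 24 months, the condition adds only about 2 to 6 percentage points to 50%.
- **That both analyses use the same people.** The primary analysis uses the modified intention-to-treat sample and the washout analysis a more restricted set. That lowers the effective correlation, so the range starts at 0.3.
- **That the visit window is an oversight.** Clarification (i) keeps it deliberately. The 26-month visit is timed from baseline, so a late 24-month visit could shorten the washout.
- **That remote visits are ignored.** Section 7.4.2.1 refits Equation 5 with totals imputed whatever the number of missing items and adds a lockdown indicator. That is a sensitivity analysis only and does not say who belongs in the main one.

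**Conclusion.** The conflict over the analysis set is established from the text and needs no assumption: 3.3 and 7.4.2 differ in both directions, and clarification (i) leaves the required scores unreconciled. How many participants are affected cannot be told from the SAP.

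The sign reading is uninformative as written. Without a persisting effect it appears half the time unconditionally. After a non-futile result it appears more often for any positive correlation, by the amounts in the table above. These figures assume ρ of 0.3 to 0.9, SD 7.5, 57 to 79 per arm, the entry condition read as p of 0.1 or more, and the linear time term of Equation 5. In two simulated cases with a non-linear time course (57 per arm, no effect), the unconditional share fell to 39.7% and 47.4%; after a non-futile result it was 89.6% and 94.7%.

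The point should be corrected, with the weight of an exploratory analysis of a secondary objective. It does not touch the primary futility conclusion.

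**What to change.** 1. Give one definition of the set in 3.3 and 7.4.2. Keep the 80mg restriction that both share. State explicitly whether the 24-month window of clarification (i) applies, how a return to 80mg after a reduction is classified, and whether three valid scores are required. The Equation 5 model allows missing visits, so the three-visit requirement is not needed.
2. Replace the sign reading with delta26* and its 95% CI, reported beside delta24* and the contrast delta26* − delta24* with its 95% CI.
3. State that the analysis is conditional on a non-futile primary result. The interval criterion is a large improvement but not full control: about 3% false readings in the −3 symptomatic case, about 5–22% if there was never an effect.
4. Carry the existing caveat on washout length into the reading: a residual symptomatic effect cannot be excluded at two months.

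The cost is SAP wording and one linear contrast from a model already planned, with fewer positive-sounding exploratory statements.
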